### Blinding

The administration of blankets will be performed in a randomized order but blinding of the patients and operators is not possible. The data analyses will be performed blinded to the sequence (“AB” or “BA”, described above).

### Data collection methods

The following data will be collected for the purpose of the research and recruitment:
From hospital records: Name, phone number, personal identification number from the Danish Civil Registration System (CPR number), diagnosis, medication prescriptions.From actigraphy (Motionlogger Micro Watch from Ambulatory Monitoring Inc. NY): Total sleep time, sleep onset latency, number of awakenings, wake after sleep onset.From diaries: The use of sleep and anxiety medications, bedtime and time of getting out of bed, number of awakenings and duration, wake after sleep onset and daytime naps including lengths registered in minutes.From six validated questionnaires: The Global PSQI Score using The Pittsburgh Sleep Quality Index (PSQI), the insomnia severity score using the Insomnia Severity Index (ISI), depressive symptoms using the Major Depression Inventory (MDI) and 6-item Hamilton Rating Scale for Depression (HAM-D_6_), patients’ self-reported symptoms using the Self-reported Symptom State Scales (SCL-28) and anxiety symptoms using the Beck Anxiety Index (BAI) [3, 25, 28–30].

### Data management

All data will be securely stored in REDCap. Using the function “identifier” in REDCap enables the full trial dataset to be anonymized when exported to the Stata IC15 and MotionLogger Analysis Software programs. Sleep data from actigraphy will not include any personal identifiers. Sleep data will be stored under the allocated ID number from REDCap.

The trial will be conducted in adherence to the Declaration of Helsinki - Ethical principles for medical research involving human subjects.

### Statistical methods

Paired, two-sided analyses will be performed. If the differences in the measures between the exposure and control periods for each patient are normally distributed, as we expect, we will use a Student’s *t* test to test the null hypotheses of no differences. For the non-normal distributions, non-parametric tests, e.g. Wilcoxon signed-rank tests or Fisher’s exact tests will be used.

All data with or without protocol violation will be included in the analysis with complete outcome data for all randomized participants. Because the analyses are based on the differences between period A and B or B and A for each patient, we will perform complete case analysis (i.e. participants with missing actigraphic data from one of the periods will be removed from the analysis). An intention to treat analysis will be performed, i.e. patients that in one or both of the periods use an “incorrect”, non-study blanket will be kept in the analyses in their randomized sequence group. We will not account for missing data by imputation.

The level of statistical significance will be set to 5%.

The randomization will determine whether the participants will begin or end with a PBB. The baseline characteristics of these two groups will be presented in a table. Baseline information on sleep will be based on The Pittsburgh Sleep Quality Index (PSQI) and the Insomnia Severity Index (ISI) and not collected via actigraphy.

There will be no wash-out period in this trial because the PBB are expected to have no residual effect persisting in the subsequent periods. This assumption is based on the biological mechanisms of the ball blanket and on clinical experience, but there are no studies to corroborate this expectation. This aspect of the design, however, is expected to lead to bias toward the null, i.e. that the study will not overestimate a potential effect of PBB. The assumption of no carry-over effect in the data will be ruled out in a preliminary test. The sum of the TST values will be calculated for the time period when using PBB and when using patients’ own duvets for each participant. This will be compared across the sequence groups by means of an independent *t* test. If this test yields a statistically significant result, the usual test for differences between the effects of treatment A or B will not be applied [31].

Data will be analysed using Stata IC15 (Stata Corp, College Station, TX, USA).

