**Fig. 2 Fig2:**
[figure not shown]
Study schedule for enrolment, intervention, and assessments

The participant timeline (Fig. 1) shows patients will meet with data collectors four times in total. Initially for the purpose of recruitment and written consent (visit 1), the second visit (Visit 2) consists of the installation and activation of actigraphs. Baseline data will be gathered using six validated questionnaires (see the “Data collection methods” section for further details). Patients will be introduced to the sleep and medication diary (Table 2) presented as a supplementary material. Data from sleep diaries will be used to aid the process of scoring sleep-wake stages, when analyzing patients’ actigraphic sleep records. Subsequently, patients are randomized into either (1) sequence “AB” or (2) sequence “BA” each lasting 4 weeks. Patients randomized to the AB sequence receive treatment A (Protac Ball Blanket™, Flexible, 7 kg) in the first 2 weeks (14 nights) and switch to treatment B (treatment as usual = regular duvet) in the second period, whereas patients that are randomized to the BA sequence receive treatment B in the first period and treatment A in the second period. This means that participants will serve as their own controls.

In both sequences, patients receive general sleep advice prior to participation [4]. The rationale behind this is to avoid behavioural irregularities between periods in order to make comparison of data possible. Patients are recommended to avoid major variations in their sleep-wake patterns from day to day during the trial. But also to avoid major variations in their sleep environment and nicotine, caffeine, alcohol and food consumption directly before bed. Patients are also advised to limit daytime naps to a maximum of 30 min.

The third visit (visit 3) at day 15 consists of a switch-over visit to either receive the intervention or treatment as usual. All six questionnaires will be repeated. Data concerning sleep and medication will be downloaded from actigraphy and collected from diaries for the first 2-week period (14 days and nights). The procedures will be repeated at the end of the study (week four = day 29) at visit 4.

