
### Sample size

The power calculation is based on data from a pilot study (*N* = 8) as we have not identified any studies investigating the effects of ball blankets on TST in depressed patients.

The main outcome will be changes in total night-time sleep with and without PBB estimated by the means of the differences between the periods for each participant. The null hypothesis is that there is no change in sleep duration. In the pilot study, the mean sleep duration appeared normally distributed and the mean sleep duration without a ball blanket was 420 min. The standard deviation of the difference between the sleep duration with and without a ball blanket was 42 min. Based on the potential clinical gains, we aim to be able to detect a change in total sleep duration of 20 min. Assuming that the differences in sleep duration with and without a ball blanket is normally distributed, we performed power calculations for a paired *t* test, and with an alfa = 0.05 and power = 0.80 the minimum required sample size is *N* = 37. To take into account dropout rates, we aim to include 45 patients.

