## Discussion

This trial has some limitations. First, we use the PSQI four times during the trial. For the purpose of screening for eligibility and again at visits 2, 3, and 4. However, PSQI is a retrospective 30-day instrument and there will be less than 30 days between assessments at visits 3 and 4 (14 days to be precise) [3]. However, there will be no overlap in the recall periods between visits, as patients are asked about their sleep quality during the past 14 days at these particular two visits using a modified version of the PSQI. This is not expected to cause any bias to the results and interpretations of these as a duration of 2 to 3 weeks is often recommended clinically to differentiate transient from persistent sleep-wake disorders [3]. Most importantly, the PSQI with a 1-month recall period will be used as suggested when screening for eligibility and again at visit 2, which will enable us to separate the transient sleep-wake problems from the persistent sleep-wake problems when recruiting patients for this trial [3].

Second, remission in the underlying depression condition may occur during the trial. In order to minimize the chance of remission and to ensure a constant intensity during both periods (AB and BA), we have chosen a short intervention period. The condition is less likely to develop radically compared to when there are long treatment periods.

Third, patients in outpatient clinics are often in need of acute treatment. Therefore, period effects may occur due to newly introduced medication or medication adjustments during the trial period. Nevertheless, patients will not be excluded from the study due to these conditions as recruitment will then become almost impossible. Besides, such conditions will be equally distributed between sequence groups A-B and B-A due to the randomization. In order to interpret the results critically, we register medication prescriptions at baseline and again in sleep diaries if any changes are made during the trial period.

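### The primary paired t test has no period term although the protocol says period effects may occur; the likely cost is lost power and possibly some bias, and a period-adjusted analysis is nearly free

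*Protocol article*

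**What the plan says.** In Statistical methods the protocol article fixes the test for all outcomes: "Paired, two-sided analyses will be performed". If the within-patient differences are normal, "we will use a Student’s *t* test to test the null hypotheses of no differences". Otherwise, "For the non-normal distributions, non-parametric tests, e.g. Wilcoxon signed-rank tests" or Fisher's exact test apply. The Abstract, the primary outcome definition and the Sample size section describe the same paired comparison. The analysis uses complete cases without imputation, so a patient lacking actigraphy in one period drops out.

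The only comparison between sequences is a preliminary carry-over test on the sum of each patient's TST values.

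The Discussion concedes that "period effects may occur due to newly introduced medication or medication adjustments during the trial period" and that depression may remit during the trial. On medication changes its answer is that "such conditions will be equally distributed between sequence groups A-B and B-A due to the randomization".

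The sample size rests on the same test: "with an alfa = 0.05 and power = 0.80 the minimum required sample size is *N* = 37".

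**The concern.** In an AB/BA crossover, a shift common to all patients between period 1 and period 2 enters the blanket-minus-duvet difference with opposite signs in the two sequences. A paired test that pools the sequences does not know which patient was in which, so it treats this systematic split as random noise. Randomisation balances the two signs in expectation, which protects the average. It does not reduce the noise, and it does not guarantee equal numbers once incomplete cases are removed.

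The carry-over test does not help. A period effect adds the same amount to every patient's sum, so it cancels when sums are compared between sequences.

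At stake are the 80% power on which N = 37 rests and, with unequal completers, the TST estimate itself. The test is written into the protocol, so this is not a detail left to an analysis plan.

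**Working it through.** **Inputs from the protocol article.** SD of the paired difference 42 min (pilot, N = 8), target effect 20 min, two-sided alpha 0.05, power 0.80, N = 37, 45 to be enrolled (Sample size); blocks of 4, 6 and 8 (Allocation); complete cases (Statistical methods).

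**Assumed.** The period effect p (period 2 minus period 1) has no stated size; 10, 20 and 30 min are used.

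**1. The plan's own figure.** Noncentrality is 20/(42/√37) = 2.90. The exact paired t test has power 0.805 at N = 37 and 0.793 at N = 36, so 37 is reproduced. It holds as stated when p = 0.

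**2. Algebra.** With treatment effect τ, the difference d centres on τ − p in AB and τ + p in BA. Hence:
- mean of d = τ + p(n_BA − n_AB)/n
- expected variance of d as the paired test estimates it = 42² + p² × 4·n_AB·n_BA/[n(n − 1)], which is about 42² + p² near balance

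**3. Near-balanced completers.** For 18 and 19 the factor on p² is 4 × 18 × 19/(37 × 36) = 1.03. Power and type I error are simulated. AB/BA of 19/18 puts the extra patient where a positive p works against the blanket; 18/19 is the mirror.

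| p (min) | SD seen by paired test | Paired power, 19/18 | Paired power, 18/19 | Period-adjusted power | Paired type I error |
|---|---|---|---|---|---|
| 0 | 42.0 | 80% | 80% | 80% | 5.0% |
| 10 | 43.2 | 78% | 80% | 80% | 4.4% |
| 20 | 46.6 | 71% | 76% | 80% | 3.1% |
| 30 | 51.8 | 61% | 70% | 80% | 1.7% |

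**4. Unequal completers.**
- 20/17, in either direction: bias p × 3/37 = 0.8, 1.6 and 2.4 min for p = 10, 20, 30.
- 22/15, in either direction: bias p × 7/37 = 1.9, 3.8 and 5.7 min. At p = 20 this is 3.78/20 = 19% of the target. Paired power is about 55% if the bias works against the blanket and 88% if it works for it; the higher figure is itself a product of the bias. Type I error is about 5.5%.
- Period-adjusted at 22/15: bias about 0, power 79%, type I error 5%.

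**5. How likely is imbalance?** Assume unstratified blocks, 45 randomised and 37 completing at random. The mean absolute difference between sequences is then 2.3 patients; it is 5 or more in 14% of runs and 7 or more in 2.5%.

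**6. Sample size after adjustment.** The adjusted test has n − 2 degrees of freedom. With equal sequences its exact power is 0.804 at N = 37 and 0.793 at N = 36, so 37 still suffices.

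**The case against.** The case for leaving the test alone has several good parts.

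- **Period effects are conceded, not predicted.** A reader might infer that the protocol expects them; it says only that they may occur. It also chose short periods to limit remission. The sleep advice ("In both sequences, patients receive general sleep advice prior to participation") is meant to keep behaviour regular between periods, so it is not evidence of a trend.
- **Medication changes are mostly not a period effect.** Changes made at different times in different patients add patient-level noise under either analysis. Only the average shift common to all patients counts as p, and 20 to 30 min would equal or exceed the treatment target.
- **The loss can be negligible.** At p = 5 and near-balance, paired power is 79.7% or 80.5% depending on direction.
- **Large imbalance is uncommon** under random dropout, and the protocol gives no reason to expect dropout to depend on sequence.
- **The pilot SD may already contain period variation**, because the pilot's period order is not stated. The loss against plan would then be smaller.

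A reader might also infer that a time trend would often pass for a blanket effect. The figures do not support that: near balance the paired test is conservative, and even at 22/15 with p = 20 its type I error is only about 5.5%. Material inflation needs something like 12/25, where it is 7%, 12.5% and 19% for p = 10, 20, 30.

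These points limit the size of the problem. They do not rescue the protocol's argument, which is sound for bias in expectation but not for precision or for chance imbalance among completers.

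**Conclusion.** The concern holds in a limited form. The primary test omits period although the protocol acknowledges that period effects are possible, and randomisation alone is not a sufficient answer. Everything quantitative depends on an assumed p, on SD 42 and on 37 completers. Near balance, the loss against adjustment is about 0 to 2 power points at p = 10, 4 to 9 at p = 20 and 10 to 19 at p = 30. Bias is at most 2.4 min at 20/17 and reaches 3.8 min at 22/15 with p = 20. The consequence is lost power and a possibly biased estimate, with little risk of extra false positives at plausible splits. It should be fixed because the remedy is almost free; the documents do not show that the planned test is bound to fail.

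**What to change.** Make the primary TST analysis period-adjusted, in either of two ways:
- compare period 1 minus period 2 differences between AB and BA by a two-sample t test and halve the contrast; or
- fit a linear mixed model with fixed treatment and period and a random patient effect.

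Report the estimate with its 95% confidence interval. Use the same approach for the other outcomes. It matters for the PSQI too: the Discussion gives visit 2 a one-month recall but visits 3 and 4 a 14-day recall, and any resulting shift falls in the period 1 change of both sequences. Where a rank test is needed, use a rank-sum test on period differences between sequences instead of the signed-rank test.

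As a minor wording point, drop Fisher's exact test from the paired fallbacks; it compares independent groups.

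**Cost.** Wording and one degree of freedom. N = 37 and data collection are unchanged, and sequence is already recorded. If there is no period effect, power is essentially the same near balance and about 79% instead of 80% at 22/15.

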The investigators allow a + 7-day non-compliance with the scheduled visit dates (2 weeks apart) in case patients experience relapse or become ill, which can hinder a physical meeting. The allocated treatment will be discontinued in all cases of patient requests, hospitalization, and alcohol or drug abuse. Patients may withdraw from the trial for any reason. The investigators may withdraw the patient from the study if the patient is unwilling or unable to wear the actigraph, as the analysis of the primary outcome data depends on these measures.

In case patients experience intolerable adverse events and other unintended effects of trial interventions or trial conduct, the reasons will be recorded in the patient’s Case Report Form (CRF) and securely stored in REDCap. All serious adverse events will be reported to the Danish Scientific Ethics Committee, in the final article, and also to Protac A/S.

The overall protocol adherence is secured by [name] and the three research assistants. Individual training of research assistants is completed before study initiation. In order to secure full data completion, we have registered all questions from questionnaires as “required” in the REDCap (REDCap 8.5.22 2019 Vanderbilt University) system. Hereby, the system will immediately remind us of any missing data when patients are present. REDCap (Research Electronic Data Capture) is a secure browser-based, metadata-driven EDC software solution and workflow methodology for designing clinical and research databases. All data from this trial will be securely stored in REDCap.

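### The analysis labelled intention-to-treat drops every randomised patient with actigraphy missing in one period, and refusing the actigraph can end a patient's participation in the whole study

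*Protocol article*

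**What the plan says.** Three parts of the protocol article bear on this.

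- **Statistical methods.** The article says "An intention to treat analysis will be performed" and explains the term by one case only: a patient who sleeps under a non-study blanket is still analysed in the randomised sequence. The same paragraph sets a complete-case rule, under which "participants with missing actigraphic data from one of the periods will be removed from the analysis", and excludes imputation. The reason given is that the analysis rests on within-patient differences between periods.
- **The practicalities of the trial.** "The investigators may withdraw the patient from the study if the patient is unwilling or unable to wear the actigraph". The reason given is that the primary outcome depends on actigraphy. The rule is discretionary and concerns the study as a whole, not only the actigraphic outcomes.
- **Allocation and Blinding.** Patients and operators are not blinded, and the outcome assessors know the sequence. Only the data analysis is blinded to sequence.

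The Sample size section allows for losses without giving a rate: "To take into account dropout rates, we aim to include 45 patients".

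**The concern.** An analysis that removes randomised patients because of something that happened after randomisation is not intention-to-treat in the usual sense. The article's definition covers use of the wrong blanket. It does not cover missing data. A reader of the results would take the label to mean that all randomised patients contribute, when the estimate describes only those with actigraphy in both periods.

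The withdrawal rule adds a second problem. A patient who will not wear the device cannot supply total sleep time, sleep onset latency, awakenings or wake after sleep onset. The same patient can still supply diaries and questionnaires. Withdrawal from the study puts those data at risk for a reason that has nothing to do with them. The decision is made by staff who know the sequence, and later blinding of the data analysis cannot undo it.

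**Working it through.** **1. The plan's own sample size.** Inputs from Sample size: "we aim to be able to detect a change in total sleep duration of 20 min"; "The standard deviation of the difference between the sleep duration with and without a ball blanket was 42 min"; and "with an alfa = 0.05 and power = 0.80 the minimum required sample size is" 37. Statistical methods gives the sidedness: "Paired, two-sided analyses will be performed". For a two-sided paired t test the noncentrality is (20/42) × √n on n - 1 degrees of freedom. Power is 79.3% at n = 36 and 80.5% at n = 37, so the stated 37 is reproduced and is not in dispute. With all 45 analysable, power is 87.8%.

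**2. How much loss the plan tolerates.** 45 - 37 = 8 patients, and 8/45 = 17.8%. This is the largest loss that leaves 37 complete pairs. It is not a forecast of drop-out.

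**3. Outcomes that do not need the actigraph.** The article lists ten secondary outcomes. Three are actigraphic: sleep onset latency, number of awakenings and wake after sleep onset. Seven are not: sedative and hypnotic use (diary), PSQI, HAM-D6, ISI, MDI, BAI and SCL-28 (questionnaires).

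**4. What the complete-case mean could hide.** Assume 8 of 45 are removed and the 37 completers have a mean difference of 20 min. If the removed patients' true mean difference is m, the mean over all randomised patients is (37 × 20 + 8 × m)/45.

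| Assumed m (min) | All-randomised mean (min) | Complete-case excess (min) |
|---|---|---|
| 20 | 20.0 | 0 |
| 10 | 18.2 | 1.8 |
| 0 | 16.4 | 3.6 |
| -10 | 14.7 | 5.3 |
| -20 | 12.9 | 7.1 |

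If the true mean over all 45 were 0 and the removed 8 averaged -20 min, completers would average 8 × 20/37 = 4.3 min. The nominal 5% test with 37 pairs and SD 42 would then reject about 9% of the time. Every value of m is an assumption.

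**5. What a mixed model would and would not repair.** Two simulated cases separate the two kinds of loss. The protocol does not give the between-patient variance, so it had to be assumed.

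- *Loss depends on observed first-period sleep.* The true effect was 20 min, and 8 of 46 patients were lost after sleeping poorly in a first blanket period. The complete-case estimate was 22.5 to 24.1 min. A mixed model with treatment, period and random patient gave about 19.5 min.
- *Loss depends on effects never observed.* Completers gained 20 min, and eight patients had duvet-period data only, with unseen effects of 0 or -20 min. With SD of differences 42 and between-patient SD 30 or 60, the mixed model gave about 20 min. This was within 0.03 min of the complete-case result, and the standard error fell by only about 1 to 2%.

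The model helps in the first case and not in the second.

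**The case against.** The other side has five good points.

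- **Patients who reject the blanket are not removed for that reason.** A reader might infer that those who cannot tolerate the blanket are the ones dropped. The document does not support this. Data with protocol violations are included, users of the wrong blanket stay in their sequence, and removal depends on missing actigraphy from a device worn in both periods. This point stands. Bias needs missing actigraphy that is itself related to treatment.
- **The complete-case rule is open and explained.** A paired test needs both periods. This stands too. Nothing is concealed, and the fault lies in the label and the analysis set.
- **The direction of bias is open.** A reader might take the 16.4 and 12.9 min figures to show that the result will favour the blanket, by 22% (20/16.4) or 55% (20/12.9). They show no such thing. They assume that the whole allowance is lost and that all eight patients share one mean effect. With m = 20 the bias is zero. Patients who leave rather than return to their duvet would push it the other way.
- **Loss of questionnaire data is not stated.** The article does not say that diaries or questionnaires already collected are discarded, and the actigraphy wording can be read as applying to the actigraphic outcomes only. The loss is a possible result of withdrawal from the study, not a stated one.
- **Sensitivity analyses may sit in an analysis plan that is not shown.** Agreed, and their absence from the article is not the point. The point is a stated label that conflicts with a stated rule, together with a stated withdrawal rule that reaches too far.

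The simulation of unobserved loss in the working shows that a mixed model is no cure for loss related to unseen effects. It does not remove the gain when loss follows observed first-period sleep.

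**Conclusion.** The point holds in limited form. The intention-to-treat label is accurate only in the sense that use of the wrong blanket does not change a patient's sequence. As regards missing data, this is a complete-case analysis. The withdrawal rule is wider than its stated reason: actigraphy is needed for the primary outcome and three secondary ones, yet withdrawal applies to the study and can end collection of the other seven.

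The size and direction of any bias are unknown. The range of 20.0 to 12.9 min illustrates one side only and rests on assumed effects in eight hypothetical lost patients. The sample size of 37 is correct. The changes are worth making because they are cheap and concern rules the article itself fixes. The material does not show that the primary result will be wrong.

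**What to change.** 1. Call the paired analysis 'complete cases, analysed as randomised', and drop the intention-to-treat label.
2. Apply exclusion for missing data outcome by outcome, so that missing actigraphy removes a patient from the actigraphic outcomes only.
3. Amend the withdrawal rule in the practicalities section. A patient who will not wear the actigraph is left out of the actigraphic outcomes and, if willing, continues the diaries and the scheduled questionnaires. This concerns data collection only and leaves the rules for stopping the allocated treatment as they are.
4. Use a mixed model with treatment, period and random patient on all available periods. It removes bias when loss depends on observed first-period sleep. It adds little precision and does not correct loss that depends on unobserved effects.
5. For that last case, add one sensitivity analysis that assumes no benefit in patients lost during the blanket period.

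The cost is revised wording, slightly more analysis work, and continued contact with a few patients at visits 3 and 4, which are already scheduled. The sample size does not change.

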### Trial design and study setting

This multicentre trial has a randomized 2-sequence, 2-period, 2-treatment crossover design. The rationale for choosing a crossover design is as follows:
Traditionally, the recruitment of depressed patients for research trials is heavily challenged due to the nature of depression, and by choosing a crossover design, we can achieve the same precision as a parallel group trial with a lower sample size [21].We further expect easier recruitment and fewer drop-outs as all patients get to try the PBB intervention compared to a parallel group design.

We are not including a washout period in the trial design for one reason:
The clinical nature and mechanism of the PBB is unlikely to have a residual effect that persists into the subsequent period, as PBBs only cause effect when patients are exposed to the product.

The data collection period lasts 4 weeks (28 nights in total) with planned inclusion of 45 patients. The study protocol adheres to the SPIRIT (Standard Protocol Items: Recommendations for Interventional Trials) reporting guidelines [22].

The trial takes place in two outpatient settings, The Mood Disorders Clinic, Aarhus University Hospital Psychiatry, Central Denmark Region, and in the Mental Health Department Odense – University Clinic, Mental Health Service, Region of Southern Denmark. Both hospitals are public university hospitals. In Denmark, public hospitals containing outpatient clinics are free of charge and treat all patients in need of urgent treatment of depression.

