### Outcomes

#### Primary outcome measure

Changes in total night-time sleep (TST) after sleep onset measured by actigraphy [time frame: 4 weeks = 28 days]. The investigators will detect the change in total night-time sleep in minutes (i.e. actual sleep time, excluding sleep latency and wakes after sleep onset) by comparing the means of the difference in total sleep time for each participant between the two periods (A and B). The night-time sleep frame is defined as sleep occurring during a 12-h night interval (21:00 to 08:59 h). The investigators designate the first sleep episode after 2100 h as the first nocturnal sleep episode; if the individual is already asleep at that time, the bedtime will be moved earlier to the first epoch of wake prior to sleep onset [26].

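### The statement that omitting the washout will not overestimate the blanket's effect holds only for a residual benefit; worsening after removal, and the questionnaire change scores, can inflate it

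*Protocol article*

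**What the plan says.** Under Trial design and study setting the article gives a single ground for having no washout ("We are not including a washout period in the trial design for one reason"), namely that "PBBs only cause effect when patients are exposed to the product". Statistical methods repeats this expectation, bases it on mechanism and clinical experience, and adds "but there are no studies to corroborate this expectation". It then says that this feature of the design "is expected to lead to bias toward the null, i.e. that the study will not overestimate a potential effect of PBB". No condition is placed on the sign or size of a residual effect.

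The primary analysis is the mean within-patient difference in actigraphic TST between the blanket period (A) and the duvet period (B): "Paired, two-sided analyses will be performed". The questionnaires listed under Secondary outcome measures (PSQI, HAM-D6, ISI, MDI, BAI, SCL-28) are handled differently. For each period the change from its first to its last visit is taken, and the changes in the two periods are then subtracted. Visit 3 is the last visit of period 1 and the first visit of period 2. The Blinding section says that patients and operators cannot be blinded.

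**The concern.** The sentence assigns a direction to a bias about which, by the article's own account, there is no study evidence. It covers a benefit that lingers into the duvet period. It does not cover sleep that becomes worse than usual once the blanket has been handed back. An unblinded patient in sequence AB gives up, halfway through, something expected to help, so the documents do not exclude that possibility.

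The sentence also speaks of the study as a whole, while the questionnaire outcomes use an estimator that behaves differently from the TST estimator. What is at stake is interpretation: if the sentence stands, a positive result could be presented as conservative, and the design does not guarantee that.

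**Working it through.** **Inputs from the article (Sample size).** SD of the within-patient difference 42 min; target effect 20 min ("we aim to be able to detect a change in total sleep duration of 20 min"); "alfa = 0.05 and power = 0.80"; N = 37, with 45 to be included.

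**The plan's own figure.** A paired t test with noncentral t gives power 0.793 at N = 36 and 0.805 at N = 37, so the stated 37 is reproduced. The sample size is not in question.

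**Assumption.** The residual effect c, in minutes of TST relative to the patient's usual duvet level, is not in the documents. It is varied below.

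**TST.** With t the true effect and equal numbers per sequence, so that period effects cancel:

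- Sequence AB (blanket, then duvet): expected A - B = t - c
- Sequence BA (duvet, then blanket): expected A - B = t
- Mean: ((t - c) + t)/2 = t - c/2

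| t (min) | c (min) | Estimate t - c/2 (min) |
|---|---|---|
| 20 | +20 | 10 |
| 20 | +10 | 15 |
| 20 | 0 | 20 |
| 20 | -10 | 25 |
| 20 | -20 | 30 |
| 0 | 0 | 0 |
| 0 | +20 | -10 |
| 0 | -20 | +10 |

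For t > 0 the estimate lies between 0 and t only if 0 ≤ c ≤ 2t. Benefit is overestimated exactly when c < 0, by |c|/2.

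**Questionnaire change scores.** Let y0, y1 and y2 be the scores at visits 2, 3 and 4, signed so that improvement is positive. Relative to the untreated level:

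- AB: y0 = 0, y1 = t, y2 = c. Blanket change minus duvet change = (t - 0) - (c - t) = 2t - c
- BA: y0 = 0, y1 = 0, y2 = t. Blanket change minus duvet change = (t - 0) - (0 - 0) = t
- Mean: (2t - c + t)/2 = 1.5t - c/2

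With c = 0, which is the article's own assumption, this is 1.5t, an overestimate of 50%. It equals t only if c = t, that is, if the benefit carries over completely. Simulation confirmed both formulas: with t = 20 and c = 0 the TST-type mean was 20.0 and the change-score mean 30.0 (about 40 in AB and 20 in BA).

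**Does the carry-over pre-test protect the sentence?** Assume a per-period TST SD of 45 to 75 min (not in the documents). The SD of the two-period sum is then √(4 × SD² - 42²), which is 80 to 144 min. With 18 and 19 patients, the power of the pre-test is about 7 to 12% for |c| = 20 and 13 to 32% for |c| = 40. It gives little protection.

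**The case against.** The strongest defence is that the paragraph concerns a blanket effect that persists into the duvet period, and for that case the stated direction is right: the formula gives 15 min instead of 20 at c = +10. The wording is also an expectation, and it follows an open admission that evidence is lacking. This stands in part. A reader might infer that the article claims the bias can only run toward the null; the text does not go that far. The explanatory clause about not overestimating is nevertheless firm and carries no condition.

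A reader might also infer that the sentence fails separately whenever the blanket has no effect. It does not. With t = 0 and c = 0 there is no bias, and with t = 0 and c > 0 the estimate moves against the blanket. Only c < 0 favours it, which is the same mechanism again.

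A third tempting reading is a large false-positive risk. With t = 0, SD 42 and N = 37, c = -10 would give significance in favour of the blanket in 10.5% of trials and c = -20 in 29.1%, against 2.5%. Those figures need a rebound averaging 10 or 20 min over all 14 nights, on an objective measure, with no direct effect. Nothing in the documents supports that. A 20-min rebound confined to three nights averages 20 × 3/14 = 4.3 min, a bias of 2.1 min.

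Finally, the choice of sensitivity analyses and of the nights that enter each period mean is commonly left to an analysis plan, which is not shown. Their absence from the article is no fault. Nor does the sentence determine any test, estimator or sample size.

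**Conclusion.** The statement is wrong as written, in a limited way. For TST it is correct for a residual effect in the direction of a real benefit with c no larger than 2t, and incorrect if sleep after removal drops below the usual duvet level, when the overestimate is half the size of the drop. Whether that happens, and by how much, is unknown; a simple return to the usual level causes no bias. This part therefore shows that the design lacks the claimed property, not that the TST result will be inflated.

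For the questionnaire outcomes the failure does not depend on a rebound. If the benefit wears off by the end of the duvet period, as the article expects, the planned contrast has mean 1.5t. This assumes balanced sequences and the same t whether the blanket comes first or second. It inflates a real effect; at t = 0 and c = 0 it creates none.

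**What to change.** Replace the sentence with one limited to residual effects in the treatment's direction. Add that worsening after removal would bias TST in favour of the blanket by half its size, and that the questionnaire change scores can overestimate the effect even without carry-over. Do not describe a positive result as conservative on this ground.

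Report the period 1 comparison of TST between the two sequences, with its 95% CI, as a supportive estimate free of carry-over. The cost is small, because the data are already collected. The drawback is precision: with 19 and 18 patients and an assumed per-period SD of 45 to 75 min, the half-width is 2.03 × SD × √(1/19 + 1/18), about 30 to 50 min against a 20-min target. It cannot decide the matter and should not be presented as doing so.

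Leaving out the first nights after the switch is optional. It addresses only a short-lived rebound and does little against one that lasts the whole period.
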